### **8.2 SECONDARY OUTCOME**

In addition to parameters such as singleton/multiple pregnancy, mode of delivery, birth weight, and gestational age, secondary outcome measures include parameters that are routinely collected as part of routine clinical health care. This includes: Data on umbilical cord clamping and respiratory function monitoring parameters, blood values, complications of prematurity, infections, and neurocognitive development of the infants, as well as influencing factors and complications in the mother.

In the experimental part of the study, the serum of the infants will be analyzed at two different time points for the presence of different pro- and anti-inflammatory as well as growth factors and subsequently investigated whether there are differences in the effect on endothelial cell homeostasis of human lung endothelial cells.

### **8.3 STUDY DESIGN**

This will be a randomized, monocentric trial with control and intervention arms and stratification by gestational age and singleton/multiple pregnancy. As far as possible, the assessment of the outcome variables will be blinded.

## **9 STUDY POPULATION**

### **9.1 INCLUSION CRITERIA**

- Birth weight < 1500 gram ("very low birth weight infant")
- Gestational age at birth >23+6 weeks
- Delivery by cesarean section
- Delivery in the tertiary care perinatal center of the University Hospital Cologne
- Written consent of the legal guardian

### **9.2 EXCLUSION CRITERIA**

- Vaginal delivery
- Fetal or maternal risk (i.e. compromise, emergency c-section)
- Congenital anomalies and/or major cardiac defects
- Placental abruption or previa with hemorrhage
- Placenta accreta or increta
- Monochorionic multiples (i.e. Di/Mo or Mo/Mo twins)
- Multiples with 3 or more infants
- Parents declined study
- Severe maternal disease (e.g. COVID-19 infection)

### **9.3 NUMBER OF PARTICIPANTS**

60 births (including approximately 30% twin births) will be included. In the case of twins, for medical reasons, only the second-born infant can be randomized. The first-born infant will receive the control treatment.

### **9.4 METHODS FOR ASSIGNING PARTICIPANTS TO TREATMENT GROUPS**

Participants will be assigned randomly to study group treatments in a 1:1 ratio according to a blocked sequence of computer-generated, pseudorandom codes. Randomization is provided as a set of opaque numbered letters by the Institute of Medical Statistics and Bioinformatics at the University of Cologne. Randomization will be stratified by:

- Gestational age: 1) 24+0 - 27 + 6 SSW, 2) > 27+6 SSW.
- Type of gravidity: 1) singleton, 2) multiple

### **9.5 SUBSEQUENT EXCLUSION OF STUDY PARTICIPANTS**

Initially included infants and mothers may be subsequently excluded from the study if

- the infant does secondarily meet one or more exclusion criteria (e.g., prenatally undiagnosed severe underlying disease),
- the informed consent of the legal guardians is withdrawn.

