## **9.6 PROCEDURE IN CASE OF NON-FEASIBILITY OF THE INTERVENTION**

If it is not possible to perform study intervention for medical reasons (despite assignment to the intervention group), the participant remains in the study (intention-to-treat principle).

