## **10 STUDY PROCEDURE**

### **10.1 SCREENING AND ELIGIBILITY ASSESSMENT**

The informed consent of the parents or legal guardians is obtained prior to birth at the Department of Gynecology and Obstetrics, according to the inclusion and exclusion criteria. Reasons for an expected premature birth are maternal (e.g. pre-eclampsia, HELLP syndrome, cervical insufficiency, amniotic infection) or fetal (e.g. intrauterine growth retardation, pathological CTG) pregnancy complications. For this purpose, pregnant women > 23+6 weeks' gestation and < 32 + 0 post menstruationem, in whom premature delivery of the infant is expected < 32 + 0 gestational age and in whom the estimated birth weight of the infant is < 1500 grams, will be informed about the study as potential study participants.

The infant will only be included in the study if the legal guardians (usually both parents, in the case of a single parent, the sole legal guardian) have given their consent after they have been informed about the nature, significance and scope of the trial in an appropriate and comprehensible way, by a physician of obstetrics and neonatology, both orally and in writing, and at the same time have declared with their consent that they agree with the recording of data that will take place within the framework of the trial. If there is a twin pregnancy, a signed declaration of consent from the legal guardians must be available for each infant.

The parents are informed that they can withdraw their consent at any time without giving reasons and without any disadvantages for their infant or themselves. The original written consent will be kept in the study folder at the study center. A copy of the written information and informed consent will be given to parents and guardians.

Since a large number of the described complications leading to premature birth can occur in acute and also unexpected ways, prenatal informed consent of both guardians is not always possible (e.g. in case of a business trip of the father). In this case, the second guardian (usually the father) is informed as soon as possible after birth. If consent is then refused, the infant will be excluded from the study.

The original of the information for the legal guardians and the written consent form will be kept in a study folder in the study center.

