10.2.1.3 PROCEDURE IN THE CONTROL GROUP DURING AND AFTER BIRTH

In the control group, delayed cord clamping (DCC) is performed by the obstetrician and neonatologist. As soon as the infant is born, the midwife or neonatologist receives the infant with the umbilical cord still intact and the APGAR clock is started. The infant will be dried and wrapped in warm towels or a sterile plastic bag (neoHelp, Vygon, Aachen, Germany) (for extremely premature infants < 1000 g birth weight). By using gentle tactile stimuli (careful stroking over the back/hands/feet), the infant's spontaneous breathing is stimulated. While performing DCC, the infant is held at the level of the maternal pelvis (=placental level) with the umbilical cord still intact, if possible. The cord is cut after at least 30 seconds, but should not extend beyond 180 seconds.

During this period, obstetrics and neonatology are allowed to stop the DCC procedure and perform an immediate umbilical cord clamping < 30 seconds (=ICC) if one of the following criteria is fulfilled:

|        |                                                                                                                                                                                                                                                                           |
|--------|---------------------------------------------------------------------------------------------------------------------------------------------------------------------------------------------------------------------------------------------------------------------------|
| Mother | 

– Hemorrhage, hemodynamic instability, or both.

– (not known) placenta praevia, placental abruption

                                                                                                                                       |
| Infant | 

– Requirement for immediate neonatal resuscitation on neonatal care unit (avital infant with no muscle tone, no spontaneous breathing > 30 seconds).

– Interrupted placental blood circulation (placental abruption, placenta praevia)

 |

Table 1: Clinical settings in which immediate umbilical cord clamping (ICC) should be considered in the control group (according to (38)).

After the umbilical cord has been cut by the obstetric physician, the infant is transferred to the neonatal resuscitation unit of the neonatology department.

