### **14.2 STUDY POPULATION**

The primary analytic dataset is the intention-to-treat (ITT) population. This includes all randomized patients evaluated according to their assigned intervention. Only participants subsequently excluded according to section 9.5 are excluded. Intercurrent events are irrelevant for this treatment rule strategy (36).

The secondary evaluation dataset is the per-protocol (PP) population. This includes all patients included in the study who were treated and observed in a substantially protocol-compliant setting.

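### Protocol 9.5 and 14.2 allow open-label removal from the ITT set for exclusion criteria first seen at delivery, and nothing says whether 9.5 or the retention rule in 9.6 prevails

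*Protocol*

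**What the plan says.** - **Removal rule (Protocol 9.5).** Infants and mothers already included may be excluded later if "the infant does secondarily meet one or more exclusion criteria (e.g., prenatally undiagnosed severe underlying disease" applies, or if guardians withdraw consent. The section sets no time limit, names no decision-maker and does not ask for blinding.
- **Analysis set (Protocol 14.2).** The primary set is ITT: "This includes all randomized patients evaluated according to their assigned intervention". The next sentence makes the exception: "Only participants subsequently excluded according to section 9.5 are excluded".
- **Exclusion criteria (Protocol 9.2).** The list includes "Fetal or maternal risk (i.e. compromise, emergency c-section", abruption or previa with bleeding, and accreta or increta.
- **Knowledge of allocation (Protocol 10.2.1.1).** The envelope is opened before birth, and everyone involved in delivery and resuscitation is told the result before the caesarean starts.
- **Retention rule (Protocol 9.6 and 10.2.1.6).** If the intervention cannot be carried out for medical reasons, "the participant remains in the study (intention-to-treat principle". Section 10.2.1.6 repeats this where the placenta cannot be delivered or the obstetric team has concerns, heavy maternal bleeding among them.
- **Control arm (Protocol 10.2.1.3, Table 1).** The reasons for clamping at once in a control infant include "not known) placenta praevia, placental abruption".

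**The concern.** An ITT set protects the randomised comparison because nothing that happens after allocation can change who is in it. Here a written rule allows membership to change after treatment, at the discretion of people who may know the arm, for events that the delivery itself can reveal. A previa that bleeds, or an accreta found when detachment of the placenta is attempted, fits the retention rule in 9.6 and also the removal rule in 9.5.

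At stake is the primary hematocrit comparison. If such infants have lower hematocrit and are removed more often from one arm, the estimated difference moves for reasons unrelated to treatment. With about 30 infants per arm, a few decisions are enough to matter.

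**Working it through.** **1. The rules side by side**

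| Event first seen at delivery | Exclusion criterion in 9.2? | Under 9.5 and 14.2 | Under 9.6 and 10.2.1.6 (EPT arm) |
|---|---|---|---|
| Abruption, or previa with bleeding | Yes | May be removed | Kept if it stops EPT |
| Accreta or increta | Yes | May be removed | Kept if it stops EPT |
| Fetal or maternal compromise | Yes | May be removed | Kept if it stops EPT |
| Deep placenta or adhesions alone | No | Not reached | Kept |

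The first three rows have two answers and the protocol ranks neither. The last row has one. So the exposed infants are a subset of the EPT failures, plus any control infant with a listed event.

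**2. The planned size reproduces**

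Inputs from 14.7: 52.1 (SD 6.6) against 57.31 (SD 7.26), difference 5.21 points, unequal-variance t test, two-sided, 80% power. The error level is not given as a number; I assume 5%, in line with the 95% intervals in 14.1. Noncentral t with Satterthwaite degrees of freedom gives 78.8% power at 28 per arm, 80.2% at 29 and 81.6% at 30. The stated 29 per arm is correct, and 60 births leave 60 − 58 = 2 spare.

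**3. Illustration of the shift**

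Let R be the mean hematocrit of the EPT infants who stay, f the fraction removed and g the deficit of the removed infants against R. No controls are removed.

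- Mean of all EPT infants: (1 − f)R + f(R − g) = R − f·g.
- Rise in the EPT mean after removal: f·g.
- With f = 3/30 = 0.10 and g = 5 to 10: rise = 0.5 to 1.0 points.
- Against the planned difference: 0.5/5.21 = 9.6%; 1.0/5.21 = 19.2%.

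The values of f and g and the absence of control removals are assumptions. The protocol gives no hematocrit for such infants. For scale, a failed-EPT infant at the control mean would sit 57.31 − 52.1 = 5.21 points below a successful one.

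**4. Upper bound**

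Section 7.3 expects that the placenta cannot be delivered with the infant in 10 to 20% of elective sections, which is 3 to 6 of 30. Suppose all of these were removed, which would mean ignoring 9.6 altogether, and that they would have been at the control mean. The all-randomised difference is then 0.9 × 5.21 = 4.69 or 0.8 × 5.21 = 4.17, while the analysed difference stays at 5.21. The overstatement is 0.52 to 1.04 points.

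A simulation (40,000 runs per setting, SD 6.6, unequal-variance t test rather than the planned ANCOVA) took no overall difference between the arms as randomised and put the failed infants 3.3 to 6.6 points lower than the other EPT infants. Removing them raised the nominal 5% error to 5.4–6.5% with 3 removed and to 6.7–11.1% with 6 removed. Keeping everyone gave 4.2–4.7%. These are ceilings, not forecasts.

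**The case against.** The strongest defence is that the protocol already keeps failed EPT. Section 9.6 is specific where 9.5 is general, and 10.2.1.6 retains the infant even when EPT stops for severe bleeding. After its exception, 14.2 adds that intercurrent events do not matter under its treatment strategy. The only example in 9.5 is a serious disease missed before birth, which allocation cannot cause, and the clause speaks of the infant, so maternal bleeding is not a natural fit.

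Much of this stands. A reader might infer that the ITT set would lose exactly the infants in whom EPT failed. The documents do not support that: retention is explicit, and deep placenta and adhesions, two of the three reasons given in 7.3, are not exclusion criteria. A reader might also infer a definite bias towards EPT. That does not follow either, because Table 1 expects bleeding, abruption and previa in controls too. It is plausible, but not shown, that attempting to deliver the placenta reveals more of these events.

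A further tempting step is to add birth weight. Section 9.1 requires "Birth weight < 1500 gram", while 10.1 screens women in whom "the estimated birth weight of the infant is < 1500 grams". But weight is an inclusion criterion, and 9.5 acts only on exclusion criteria and consent. Neither 9.5 nor 14.2 removes a randomised infant who proves heavier, so this does not support the point.

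What the defence does not remove: the operative words of 9.5 cover any exclusion criterion, the example is only an example, and the lead-in names mothers as well as infants. An infant excluded under 9.5 has already left the set to which the treatment strategy in 14.2 applies.

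**Conclusion.** The point holds as a conflict of rules that leaves the primary analysis set open to unblinded, post-randomisation decisions. It concerns only delivery events that are also listed exclusion criteria. The comparison could be biased, possibly in favour of EPT; direction and size cannot be established from the protocol. The 0.5 to 1.0 points (about 10 to 19% of 5.21) depend on three assumptions: 3 of 30 EPT infants removed, no controls removed, and a deficit of 5 to 10 points. The planned sample size is not in question.

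**What to change.** 1. In 9.5 and 14.2, limit removal from the ITT set to (a) guardian consent withdrawn, or refused by the second guardian after birth as 10.1 provides, and (b) a congenital anomaly or major cardiac defect present before randomisation and confirmed by someone who does not know the allocation.
2. State that all other exclusion criteria apply only until the envelope is opened, and that later events stay in the ITT set under 9.6.
3. Report every removal by arm with its reason, and add a sensitivity analysis that includes excluded infants whose data may be used.

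This is amendment wording and changes no care at delivery. The small cost is that a few infants outside the ideal target population stay in the primary analysis.

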## **9.6 PROCEDURE IN CASE OF NON-FEASIBILITY OF THE INTERVENTION**

If it is not possible to perform study intervention for medical reasons (despite assignment to the intervention group), the participant remains in the study (intention-to-treat principle).

## **9.7 APPROACH TO DICHORIAL TWIN PREGNANCY**

For obstetric reasons, birth of both twin infants each with their own placenta is not applicable in a majority of dichorial twin birth.

However, if the inclusion criteria of the study are basically fulfilled in case of twin pregnancy, dichorial twins can also be included in the study.

In this case, a delayed cord clamping (DCC) procedure is always performed for twin 1 (defined as the baby that the obstetrician develops first after caesarean section).

Twin 2 is randomized to receive either EPT or DCC depending on the randomization assignment. The firstborn twin will be recorded with respect to the primary outcome measure and, as far as possible, with respect to the secondary outcome measures.

The second-born randomized twin will be assigned to the neonatal resuscitation unit, which will allow measurement of all target criteria, including respiratory function monitor.

## **9.8 PROCEDURE IN CASE OF MISSING HEMATOCRIT MEASUREMENT**

If no hematocrit was determined in the first 24 hours of life (e.g. due to death of the participant within the first hours of life), the other target values of the study participant will still be recorded and evaluated separately.

## **10 STUDY PROCEDURE**

### **10.1 SCREENING AND ELIGIBILITY ASSESSMENT**

The informed consent of the parents or legal guardians is obtained prior to birth at the Department of Gynecology and Obstetrics, according to the inclusion and exclusion criteria. Reasons for an expected premature birth are maternal (e.g. pre-eclampsia, HELLP syndrome, cervical insufficiency, amniotic infection) or fetal (e.g. intrauterine growth retardation, pathological CTG) pregnancy complications. For this purpose, pregnant women > 23+6 weeks' gestation and < 32 + 0 post menstruationem, in whom premature delivery of the infant is expected < 32 + 0 gestational age and in whom the estimated birth weight of the infant is < 1500 grams, will be informed about the study as potential study participants.

The infant will only be included in the study if the legal guardians (usually both parents, in the case of a single parent, the sole legal guardian) have given their consent after they have been informed about the nature, significance and scope of the trial in an appropriate and comprehensible way, by a physician of obstetrics and neonatology, both orally and in writing, and at the same time have declared with their consent that they agree with the recording of data that will take place within the framework of the trial. If there is a twin pregnancy, a signed declaration of consent from the legal guardians must be available for each infant.

The parents are informed that they can withdraw their consent at any time without giving reasons and without any disadvantages for their infant or themselves. The original written consent will be kept in the study folder at the study center. A copy of the written information and informed consent will be given to parents and guardians.

Since a large number of the described complications leading to premature birth can occur in acute and also unexpected ways, prenatal informed consent of both guardians is not always possible (e.g. in case of a business trip of the father). In this case, the second guardian (usually the father) is informed as soon as possible after birth. If consent is then refused, the infant will be excluded from the study.

The original of the information for the legal guardians and the written consent form will be kept in a study folder in the study center.

### **10.2 PROCEDURE IN CONTROL/INTERVENTION GROUP**

The trial consists of 3 periods.

The first period will start shortly before the birth of the infant with a randomized assignment of the infant to the intervention or control group as well as the implementation of EPT immediately after birth

or delayed umbilical cord clamping and extended monitoring of vital parameters during neonatal resuscitation.

The second period comprises the hospital stay and includes the documentation of clinical parameters and blood tests of the infants, as well as of the mothers. This period ends with an individually variable duration at discharge of the infant and the mother.

The third period occurs at a corrected age of  $24 \pm 2$  months and includes the assessment of the BSID III.

## **10.2.1 FIRST STUDY PERIOD**

### **10.2.1.1 BEFORE THE BIRTH**

Medical records of mothers who have been informed about the study and for whom consent to study participation has been obtained from the legal guardians will be labeled on the patient's record ("Participant EXPLAIN Trial"). Obstetrics will inform Neonatology of the mother's impending delivery or the impending delivery of a study participant. The neonatologist and the obstetrician in charge will now make sure that the informed consent form signed by both guardians is available. The sealed randomization envelopes for the study participants are kept in a location accessible and known to the neonatologists in charge at the neonatal intensive care unit and are now opened in his presence of both physicians. Initially, the last name, first name and date of birth of the infant are handwritten on the randomization form, which is later covered with a patient label. This allows the unique assignment of the randomization ID to an infant.

The randomization order is communicated before the start of the cesarean section, to all staff involved in delivery and neonatal resuscitation.

The neonatology staff must ensure that the recording of additional study-related parameters can take place. For this purpose, the extended respiratory function monitor is prepared and a kitchen weighing scale is provided on the resuscitation unit.

### **10.2.1.2 PROCEDURE FOR TWIN PREGNANCY PRIOR TO BIRTH:**

Similar to the procedure described above, the obstetrician and neonatologist must ensure that a signed informed consent form for study participation is available for each infant. A randomization envelope will be opened prior to delivery. The randomization envelope is only valid for **twin 2** at delivery. At the birth of **twin 1**, the procedure of the control group ("delayed cord clamping" (DCC)) described in section 9.7 is always chosen (independent of the randomization envelope for **twin 2**). **Twin 1** is defined as the child that the obstetrician develops first after caesarian section.

Analogous to the procedure described above, the surname, first name, and date of birth of second twin is noted on the randomization letter or later pasted over with patient label.

Before the start of the cesarean section, the randomization notification is communicated to all staff involved in the delivery and neonatal resuscitation of the infant. It must be ensured in advance that the

randomized infant (= twin 2) is transferred to the neonatal resuscitation unit with the extended respiratory function monitoring (including NIRS).

10.2.1.3 PROCEDURE IN THE CONTROL GROUP DURING AND AFTER BIRTH

In the control group, delayed cord clamping (DCC) is performed by the obstetrician and neonatologist. As soon as the infant is born, the midwife or neonatologist receives the infant with the umbilical cord still intact and the APGAR clock is started. The infant will be dried and wrapped in warm towels or a sterile plastic bag (neoHelp, Vygon, Aachen, Germany) (for extremely premature infants < 1000 g birth weight). By using gentle tactile stimuli (careful stroking over the back/hands/feet), the infant's spontaneous breathing is stimulated. While performing DCC, the infant is held at the level of the maternal pelvis (=placental level) with the umbilical cord still intact, if possible. The cord is cut after at least 30 seconds, but should not extend beyond 180 seconds.

During this period, obstetrics and neonatology are allowed to stop the DCC procedure and perform an immediate umbilical cord clamping < 30 seconds (=ICC) if one of the following criteria is fulfilled:

|        |                                                                                                                                                                                                                                                                           |
|--------|---------------------------------------------------------------------------------------------------------------------------------------------------------------------------------------------------------------------------------------------------------------------------|
| Mother | 

– Hemorrhage, hemodynamic instability, or both.

– (not known) placenta praevia, placental abruption

                                                                                                                                       |
| Infant | 

– Requirement for immediate neonatal resuscitation on neonatal care unit (avital infant with no muscle tone, no spontaneous breathing > 30 seconds).

– Interrupted placental blood circulation (placental abruption, placenta praevia)

 |

Table 1: Clinical settings in which immediate umbilical cord clamping (ICC) should be considered in the control group (according to (38)).

After the umbilical cord has been cut by the obstetric physician, the infant is transferred to the neonatal resuscitation unit of the neonatology department.

The infant is given initial care in accordance with the clinic's internal standards: The infant is further placed in warm towels or in an occlusive polyethylene wrap (NeoWrap™, Fisher&Paykel Healthcare Limited, Auckland, New Zealand) for temperature management or remains wrapped in the sterile plastic sheet (neoHelp, Vygon, Aachen, Germany), it is placed in the left lateral position (so-called "comfort position") and the neonatologist initiates respiratory support using a CPAP mask according to a standardized internal protocol. At the same time the nurse establishes a standardized monitoring which includes transcutaneously measured blood oxygen saturation, heart rate, respiratory rate and tidal volumes.

As an additional monitoring parameter, regional cerebral oxygen saturation (rScO2) will be measured using near infrared spectroscopy (NIRS). The measurement will be established non-invasively via the additional application of a self-adhesive neonatal NIRS sensor to the midline forehead of the infants. It involves the recording of only one channel (1-channel NIRS), the second channel is not recorded. The

measurement is recorded for the duration of neonatal resuscitation approximately 60 minutes, after which the sensor is removed.

The arrangement in the context of the neonatal resuscitation of the control group is shown in Figure 1.

[figure not shown]

Figure 1: Schematic illustration of initial treatment of infants in the control group

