#### **14.4.4 TARGET VARIABLES RECORDED IN PARTICIPANTS OF CONTROL (DCC) GROUP AND FIRST TWIN**

- Time to umbilical cord clamping after DCC (sec).

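### In the control arm, the resuscitation criterion for clamping before 30 seconds requires more than 30 seconds without breathing, so it cannot be met in the window it is meant to open

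*Protocol*

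**What the plan says.** All the relevant text is in Protocol section 10.2.1.3, which describes the control procedure.

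- **Clock.** The section says that "As soon as the infant is born, the midwife or neonatologist receives the infant with the umbilical cord still intact and the APGAR clock is" set running at that point. Time therefore runs from birth.
- **Ordinary rule.** "The cord is cut after at least 30 seconds, but should not extend beyond 180 seconds".
- **Early exit.** "During this period, obstetrics and neonatology are allowed to stop the DCC procedure". What the section lets them do instead is to "perform an immediate umbilical cord clamping < 30 seconds (=ICC) if one of the following criteria is fulfilled". The list of criteria is Table 1.
- **First infant criterion.** A need for immediate resuscitation, described in brackets as "avital infant with no muscle tone, no spontaneous breathing > 30 seconds".
- **Second infant criterion.** "Interrupted placental blood circulation (placental abruption, placenta praevia"), with no time threshold. The maternal criteria (bleeding or circulatory instability, and unrecognised praevia or abruption) have none either.

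Sections 9.7, 10.2.1.2 and 10.2.1.5 apply the same control procedure to every first twin, whatever the envelope says for the second twin. Section 14.4.4 records "Time to umbilical cord clamping after DCC (sec") for controls and first twins.

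**The concern.** The exit exists so that a lifeless infant can be separated from the placenta before the DCC minimum is reached. As worded, its qualifying condition takes longer to establish than the window in which the exit may be used. The text then gives no clear status to a control infant, or a first twin, who is clamped early because of absent tone and breathing. It could be a permitted immediate clamping or a departure from the protocol.

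Two things are at stake. First, this is a delivery-room rule for the most depressed infants, and staff should be able to apply it without choosing between readings. Second, section 6.3 justifies the trial by the need to compare extrauterine placental transfusion (EPT) with a defined clamping strategy, because the retrospective cohort had mixed immediate clamping, DCC and cord milking in one group. The boundary between DCC and permitted immediate clamping is part of that definition, and this clause blurs it.

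**Working it through.** **Inputs, all from section 10.2.1.3.** Let t be the time of clamping in seconds after birth, and a(t) the time without spontaneous breathing by then.

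1. Ordinary DCC: 30 ≤ t ≤ 180.
2. Permitted early exit (ICC): t < 30.
3. First infant criterion: a(t) > 30.
4. The clock starts at birth, so a(t) ≤ t.

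**Check from birth.** Conditions 3 and 4 give t ≥ a(t) > 30. Condition 2 gives t < 30. No t meets both. A scan of t from 0 to 180 seconds in half-second steps also found no such time.

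**What happens once the criterion is met.** Then t > 30. Up to 180 seconds, clamping is already covered by condition 1, and by condition 2 it can no longer be called ICC. The criterion therefore opens nothing that the ordinary rule does not already allow.

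**Opening words of the exit.** The sentence before the exit describes cutting the cord between 30 and 180 seconds. If the period referred to is that window, an act at t < 30 lies outside it. If the period is the whole DCC procedure from birth, the phrase is harmless, but conditions 2 and 3 still exclude each other.

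**Alternative readings.**

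- *The limit of 30 seconds runs from recognition of the problem.* Recognition comes at some t₀ > 30 and clamping before t₀ + 30. Such a clamp comes after the DCC minimum, so the act labelled ICC would also satisfy the minimum for DCC. The label would no longer separate the two.
- *Absent tone alone is enough.* The criterion could then be met at t < 30, but the breathing qualifier would do no work. The text does not say that either sign suffices.

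**Criteria not affected.** Interrupted placental circulation and the maternal criteria have no duration attached and can be present at any t < 30.

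**Reach of the clause.** The synopsis plans 30 births per arm and up to 30% twin pregnancies among 60 births. That is 0.30 × 60 = 18 first twins, so the control procedure governs up to about 30 + 18 = 48 infants. This counts infants under the rule, not infants who would meet the criterion. The documents give no figure for the latter.

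**Sample size.** Section 14.7 compares 52.1 (SD 6.6) with 57.31 (SD 7.26). At a two-sided 5% level (assumed, since the section gives no number), the unequal-variance t test has power 0.788 with 28 per arm and 0.802 with 29. The stated 29 per arm is reproduced, and clamping time is not among its inputs.

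**The case against.** The strongest reply is that the clause is permissive. It allows the team to stop, and the table caption only asks that immediate clamping be considered. The leading words of the criterion are the need for immediate resuscitation, and the 30-second phrase is a bracketed description. Clinicians would act on judgement, and after 30 seconds nothing conflicts because the cord may be cut anyway. The population also excludes fetal compromise and emergency section, so such infants should be few. Much of this stands: it limits the practical consequence and rules out the claim that teams are ordered to wait. It does not remove the contradiction, because the bracket is the only description the protocol gives of that criterion and it cannot be true before 30 seconds.

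A reader might infer more than the documents support:

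- *That the whole infant exit fails.* It does not. Only one of the two infant criteria has a time threshold.
- *That the per-protocol comparison becomes selective.* Section 14.2 defines that secondary set as "This includes all patients included in the study who were treated and observed in a substantially protocol-compliant setting". This leaves latitude, and nothing says that infants clamped early under Table 1 are dropped. Detailed membership rules are commonly left to a statistical analysis plan, which is not shown.
- *That reported rates of immediate and delayed clamping are distorted.* No such rate is a listed target variable. Section 14.4.4 asks for time in seconds, which is recorded whatever the label.
- *That the number of affected controls can be estimated.* The documents give no basis for one. Being depressed at birth is also not the same as being clamped before 30 seconds solely for this reason.

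**Conclusion.** The contradiction is certain on the text as it stands, with time counted from birth as section 10.2.1.3 indicates. The set of clamping times that satisfy both the exit window and the first infant criterion is empty. It is a wording fault in one criterion of a safety-relevant rule, and the reference to the period sharpens it. It does not show that the design, DCC of 30 to 180 seconds with an early exit, is faulty.

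The primary analysis is by intention to treat (section 14.2), and membership of that set does not depend on clamping time, so it is unaffected. What remains unclear is the status of a control infant or first twin clamped before 30 seconds for absent tone and breathing. The number of such infants is unknown. The point is worth correcting because the rule is used in the delivery room and the correction is small.

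**What to change.** The clinical team should reconcile, in section 10.2.1.3 and Table 1, the ICC window of less than 30 seconds with the breathing qualifier of more than 30 seconds, so that the exception can be applied. The reference to the period should be made to agree with the result. The reconciled text should make clear whether a control infant or first twin clamped early for this reason has used a permitted exit or deviated from the protocol. Which time rule is right is a clinical decision, and this review does not propose one.

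The cost is one table line and a small edit to the sentence that introduces it, submitted to the ethics committee as section 13 requires for protocol changes. Clamping time is already collected under section 14.4.4. Neither the primary analysis nor the sample size changes, and the point does not depend on any added text in section 14.2.
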